#### Registers and logged data

Medical data (morbidity, mortality, recurrence rate, biomarkers) will be obtained from medical journals, and socioeconomic data and health care costs (visits, pharmaceuticals) will be collected from medical registers up to six months after the intervention for a cost-effectiveness analysis of the intervention. Logged data on symptom reports and self-care advice accessed (adherence to the intervention) including frequencies of symptoms and generated alerts will be collected.

#### Interviews about feasibility and acceptability

On to two weeks following the intervention all the patients in the intervention group are interviewed via telephone. Interviews are based on a semi-structured interview guide exploring the feasibility and acceptability of the app, the content of the self-care advice, and technical or other problems encountered when using the system.

#### Interviews about participatory and meaningful care

Eighty patients (40 with breast cancer and 40 with prostate cancer) from both the intervention groups and the control groups will be interviewed face to face and individually about their experiences of participatory and meaningful care. The focus will be to explore how patients perceive their life situation in relation to the disease and how involved they felt in their care during the treatment. The interviews will be conducted three months after the end of treatment.

Health care professionals involved in the care of the patients in the intervention group will be interviewed via focus groups about their perceptions of the overall use of the mobile phone system and how the intervention might enhance participatory care. Special focus will be on symptom assessment and care interventions initiated because of the alert system, transfer of information and generation of alerts, and lastly the content and delivery of the self-care advice. We believe that the interaction between health care professionals in focus group interviews will give deep insights into the complexity of this phenomenon.

### Sample size calculation

The sample size is estimated from the results of the effect study including patients with prostate cancer, Sundberg et al. [56] With an effect size (Cohen’s d) difference of 0.54 in the primary outcome (urinary symptom) with 90% power at *p* < 0.05, 71 patients in each group are needed. A similar study with an expected effect size (Cohen’s d) difference of 0.20 in the primary outcome (symptom improvement) with 85% power at *p* < 0.05 with five repeated measurement needed 133 patients in each group [40]

### Statistical analysis

Data will be analysed using the IBM SPSS statistical software package (version 24.0.) Analysis will be performed according to the intention-to-treat, ITT principle, and the main aim will be to examine differences between and within groups and to investigate independent variables that may explain the outcome. The analysis will include standard descriptive statistics, and inferential analyses based on linear mixed-effect models accounting for repeated measurements [57].

Furthermore, latent class analysis will be used for each person and across the group of patients to identify groups that share characteristics with different components related to the intervention and its outcome [58]. Analyses will be performed in collaboration with a consultant statistician and a health-economist.

### Qualitative analysis

Interviews with patients and health care staff will be transcribed verbatim and analysed through inductive and deductive qualitative content analysis according to Elo and Kyngäs [59].

## Discussion

For some time now, mHealth has been predicted to be a future disruptive innovation which may revolutionise the way health care is organised [60–63]. The development and implementation of digital solutions have been encouraged by policymakers as they have been anticipated to decrease the rising health care costs which are due to an ageing population and technical advances in treatments [60, 62]. However, a plethora of articles are concerned with why the vast majority of eHealth, tele health or mHealth projects fail [45, 64]. Authors have called for studies which can provide solid and generalizable results, as well as studies considering context, values and more qualitative aspects of health technology evaluation and implementation [65–67].

Studies on clinical outcomes and cost-effectiveness of apps are sparse [46]. Since the launch of this study, promising results have emerged indicating that mHealth can have a positive effect on cost-effectiveness as well as patient safety. Basch [68] found that monitoring PROM via a computer tablet during cancer treatment improved HRQoL and resulted in fewer admissions to an emergency room or hospitalisations compared to the control group. This suggests that mHealth could function as a cost-effective method to promote communication between patients and clinicians, and to enable health care staff to tailor the care to the individual patient’s needs. In a study by Drott [69] the results showed that reporting side effects during treatment for colorectal cancer via a mobile phone based system reinforced the patient’s experience of being involved in their care.

The results of this study will provide helpful knowledge and insights into the effects of using an app for monitoring and managing symptoms and side effects during cancer treatment in a population consisting of both breast and prostate cancer patients. The size and characteristics of the cohorts will allow inferences on differences in effect between sex/diagnosis to be drawn, factors which have been found to influence attitudes and usage of mobile health technologies [70–73].

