**Method:**

The study is a prospective, randomised, controlled trial for each patient group and it is based on repeated measurements. Patients are consecutively included and randomised. The intervention groups report symptoms via the app daily, during treatment and up to three weeks after end of treatment, as a complement to standard care. Patients in the control groups receive standard care alone. Outcomes targeted are symptom burden, quality of life, health literacy (capacity to understand and communicate health needs and promote healthy behaviours), disease progress and health care costs. Data will be collected before and after treatment by questionnaires, registers, medical records and biomarkers. Lastly, participants will be interviewed about participatory and meaningful care.

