### Aim and hypothesis

This study aims to evaluate the effects of the interactive ICT platform (Interaktor) developed for this project, on patients with breast cancer during neo adjuvant chemotherapy treatment and patients with locally advanced prostate cancer during treatment with radiotherapy respectively. The main hypothesis is that the use of the platform will improve clinical management, reduce costs and promote safe and participatory care. Furthermore, the study population enables investigation of whether the intervention effects are generic. The specific research questions are:Will using the app during treatment for breast and prostate cancer respectively:
Minimize symptom burden?Enhance participatory and meaningful care?Improve the capacity to access, understand, communicate and use health information for health promoting behaviours?Impact the QoL positively, or affect disease progress and health care costs?
2.How does a person’s inner strength (sense of coherence) influence intervention effects?3.How feasible, user-friendly and accepted is the platform according to patients and health professionals?4.Are there any differences in study outcomes regarding diagnosis?

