### Prostate cancer study

Data are collected during 20 weeks, at three time points; baseline, end of treatment and three months after the end of treatment, see SPIRIT study flow chart in Fig. 2. Patients are recruited from two clinics in Stockholm County Council in Sweden; the Department of Oncology at Karolinska University Hospital and the Department of Oncology Södersjukhuset. Recruitment began in August 2015 and completion for recruitment is expected in August 2017. A sample of 150 prostate cancer patients will be recruited. Inclusion criteria are; patients diagnosed with prostate cancer, scheduled to receive curative radiotherapy for at least five weeks. Exclusion criteria are: inability to read or understand Swedish, or having a known severe cognitive disability. Patients scheduled for radiotherapy are consecutively identified for eligibility by one of the researchers by screening of the booking lists. Eligible patients are sent a letter with information about the study and contacted by one of the researchers via telephone approximately a week before their first treatment appointment. Those who agree to participate sign a consent form and fill out the baseline assessment questionnaire before being assigned to either the intervention or control group by a sequence of sealed envelopes with equal distribution among the two groups [48].

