#### Intervention and standard care

All patients receive standard treatment and care according to clinical guidelines and the protocol of the clinic where they are treated. This includes radiotherapy five days a week, with or without a combination of two sequences of brachytherapy, and regular contact with an assigned oncology contact nurse who can be contacted during office hours. The patients in the intervention group download the app onto their own smartphone or tablet; alternatively they may borrow such a device from the research group. They are instructed on how to use the app for reporting symptoms and start reporting in the app on their first day of radiotherapy. They then report daily, during weekdays, and three weeks following the last treatment. The total time for reporting is between eight to 11 weeks depending on whether the treatment is a combination treatment or not. The nurses at the clinic receive instructions and training on how to use the platform, including the alert system, and how to monitor the patients´ reports. Reporting in the app is a complement to the usual care and patients are encouraged to report before 3 PM as reports and alerts are managed during office hours (7 AM-4 PM). If emergency health care attention is needed the patients are instructed to contact the health care according to the standard procedure at the oncological clinic.

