#### Intervention and standard care

All patients receive standard treatment and care according to clinical guidelines and the protocol of the clinic where they are treated. Standard treatment and care consist of neo adjuvant chemotherapy and regular visits to the physician and the oncology contact nurse prior to every treatment occasion. The patients in the intervention group download the app onto their own smartphone or tablet; alternatively they may borrow such a device from the research group. They are instructed on how to use the app for reporting symptoms and start reporting in the app on their first day of chemotherapy. They then report daily, during weekdays, and two weeks following the last treatment, alternatively until the day of surgery. The total reporting time is approximately 18 weeks. Reporting in the app is complementary to the usual care and patients are encouraged to report before 3 PM as the reports and alerts are managed during office hours (7 AM- 4 PM). If emergency health care attention is needed the patients are instructed to contact the health care according to the standard procedure at the oncological clinic.

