### Primary outcomes

#### Questionnaires

Outcomes concerning HRQoL, symptom distress, perception of individual care, sense of coherence and health literacy will be collected through validated self-report questionnaires;EORTC-QLC-C30 (including disease-specific module PR-25 in the prostate study) for the evaluation of HRQoL [50].The Memorial Symptom Assessment Scale (MSAS) a 32-item questionnaire for measuring symptom prevalence, characteristics and distress (Breast cancer study only) [51].The Individual Care scale (ICS): a 24-item self-measurement of perception of individual care [52].The Sense of Coherence Scale a 13-item questionnaire for measuring overall coping ability (inner strength) [53, 54].The Health literacy scale: a ten-item questionnaire assessing functional, communicative and critical health literacy [55].

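### The Discussion claims inference on effect differences by sex or diagnosis, which the two-trial design cannot attribute and the sample size was not set for

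*Protocol article*

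**What the plan says.** The Discussion closes with the claim that "The size and characteristics of the cohorts will allow inferences on differences in effect between sex/diagnosis to be drawn". Under Aim and hypothesis the article says that "the study population enables investigation of whether the intervention effects are generic", and the fourth research question asks: "Are there any differences in study outcomes regarding diagnosis".

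The design is described in the abstract's Method paragraph: "The study is a prospective, randomised, controlled trial for each patient group". The prostate section says "A sample of 150 prostate cancer patients will be recruited", and the breast section gives the same number. Allocation is equal in both trials. The Sample size calculation section derives 71 per group from an effect of 0.54 in a urinary symptom outcome, taken from an earlier study in prostate patients. It also cites a similar study sized for an effect of 0.20. No figure is given for a comparison of effects between the two trials.

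**The concern.** The sentence rests on two supports, the size of the cohorts and their characteristics. The article's own facts weaken both.

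On characteristics, randomisation takes place within each trial. It protects each trial's arm comparison. It does not protect the explanation of why two arm comparisons differ. Where several features change together between the trials, no model can say which of them produced a difference in effect.

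On size, a trial that is adequate for its own effect is not thereby adequate for a difference between two such effects. That contrast has twice the variance.

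At stake is how the comparison will be read. A clear difference invites a statement about sex or diagnosis. A non-significant one invites the statement that the platform works alike everywhere. The design supports neither. The randomised comparisons within each trial are not affected.

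**Working it through.** **1. What changes between the trials.** From the two study descriptions, the two sections on intervention and standard care, the two app descriptions and the Questionnaires section:

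| Feature | Prostate trial | Breast trial |
|---|---|---|
| Treatment | curative radiotherapy | neoadjuvant chemotherapy |
| App symptom set and alert rules | own version | own version |
| Reporting time | "The total time for reporting is between eight to 11 weeks" | "The total reporting time is approximately 18 weeks" |
| Data collection | 20 weeks | 30 weeks |
| Sex | all male | men and women eligible, no number of men planned |
| Trial-specific scale | PR-25 | MSAS |
| Scales with no trial restriction | C30, individual care (ICS), sense of coherence (SOC), health literacy | the same |

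Diagnosis is completely aliased with treatment, app version and reporting time. Sex is almost completely aliased with them. The instruments are only partly separate.

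**2. The plan's own figure.** For two means with d = 0.54, 90% power and two-sided 5%:

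n per group = 2(1.960 + 1.282)² / 0.54² = 2 × 10.51 / 0.2916 = 72.1, so 73.

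The stated 71 agrees within two patients. A one-sided test would give 59 and does not fit. With 75 per arm, power for the within-trial effect is 91%.

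**3. The between-trial contrast.** In SD units each trial's effect has variance 1/75 + 1/75 = 2/75. The difference between two independent effects has variance 4/75, so SE = √(4/75) = 0.231. The 95% half-width is 1.96 × 0.231 = 0.45.

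Power for a true difference D is Φ(D/SE − 1.96):

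- D = 0.54 (full planned effect in one trial, none in the other): Φ(2.338 − 1.960) = 65%.
- D = 0.27 (half the planned effect): Φ(1.169 − 1.960) = 21%.
- Difference detectable with 80% power: (1.960 + 0.842) × 0.231 = 0.65.

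Patients needed for 80% power with this analysis, from 4(1.960 + 0.842)²/D² per cell: 108 per cell (432 in total) for 0.54, and 431 per cell (1,724 in total) for 0.27. The plan has 300 in total.

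**4. Allowing for repeated measurements.** The Statistical analysis section plans linear mixed-effect models, and each trial has a baseline and two later time points. The article gives no correlation between visits, so a range of 0.3 to 0.7 is assumed, with the same correlation ρ between any two visits. Baseline adjustment multiplies the SE by √(1 − ρ²). Averaging the two follow-up visits as well gives √((1 + ρ)/2 − ρ²).

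| Analysis | ρ | SE | Power, D = 0.54 | Power, D = 0.27 | Detectable at 80% |
|---|---|---|---|---|---|
| Unadjusted, one visit | – | 0.231 | 65% | 21% | 0.65 |
| Baseline-adjusted, one visit | 0.3 | 0.220 | 69% | 23% | 0.62 |
| | 0.5 | 0.200 | 77% | 27% | 0.56 |
| | 0.7 | 0.165 | 91% | 37% | 0.46 |
| Baseline-adjusted, mean of two visits | 0.3 | 0.173 | 88% | 35% | 0.48 |
| | 0.5 | 0.163 | 91% | 38% | 0.46 |
| | 0.7 | 0.139 | 97% | 50% | 0.39 |

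Even in the most favourable row the 95% half-width is 1.96 × 0.139 = 0.27. An observed difference of exactly zero would still be compatible with a true difference of half the planned effect.

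**The case against.** Several points on the other side are fair.

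- **Sex and instruments are not fully confounded.** A reader might infer that they are. The breast trial admits men, and four scales carry no trial restriction, so a common outcome exists. This stands. It does not restore attribution: no number of men is planned, and shared scales do not separate diagnosis from treatment, app version or reporting time.
- **The comparison is not underpowered in every case.** A reader might take 65% power, or a detectable difference of 0.65, as fixed facts. They belong to a crude single-visit analysis, and the plan is for repeated-measures models. With adjustment, a difference as large as the whole planned effect may well be detectable. This stands. A difference of half that size remains out of reach in every variant, and dropout would lower all the figures.
- **The aim about generic effects need not go.** A reader might conclude that it should be deleted. The article poses it as something to investigate. Testing one platform in two quite different settings is a reasonable way to look at generalisation. This stands.
- **The feared misreading is not in the text.** Nowhere does the article say that non-significance will be called a generic effect. Sex and diagnosis are written as one joined term, and the fourth research question mentions diagnosis only. This is right, and the risk is one of later interpretation.
- **The cross-trial model may be specified in a document not shown.** Its absence is therefore no finding. The point here is a statement that the article does make, and no later model could make it true.

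**Conclusion.** The Discussion sentence claims more than the design can give. A between-trial difference in effect would describe two care settings, each a bundle of diagnosis, treatment, app version and reporting time. It could not be assigned to sex or to diagnosis alone. This conclusion follows from the article's own descriptions and does not depend on power.

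On size, the cohorts were set for a within-trial effect. For a difference of 0.54, power is 65% unadjusted and about 69–97% with adjustment. For 0.27 it is about 21% unadjusted and at most about 50%. These figures assume 75 patients per cell, no dropout, a two-sided 5% test and, for the adjusted analyses, correlations of 0.3 to 0.7. They use 0.54 only as a yardstick, since the article gives no expected effect on any shared scale.

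The correction is worth making because it limits what may be concluded on a stated research question. The within-trial comparisons stand.

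**What to change.** Replace the Discussion sentence and qualify the fourth research question, so that the text says:

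- The two trials are analysed separately, and the cross-trial comparison is exploratory.
- It is limited to the scales used in both trials: C30, individual care, sense of coherence and health literacy.
- It is reported as the difference between the two arm effects with a 95% confidence interval.
- It describes a contrast between two care settings (diagnosis, treatment and app version together) and cannot be attributed to sex or diagnosis alone.

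Keep the question whether effects are generic under Aim and hypothesis. Add that a non-significant difference will not be taken as evidence of a generic effect, and that the width of the interval will be considered.

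The cost is a change of wording in the Discussion and in Aim and hypothesis. It needs no further patients or data.

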## Abbreviations

EORTC QLQ-C30: European Organisation for Research and Treatment of Cancer Core Quality-of-Life
HRQL: Health-Related Quality of Life
ICT: Information Communications Technology
ITT: Intention-to-treat
MRC: Medical Research Council
MSAS: Memorial Symptom Assessment Scale
PROM: Patient Reported Outcome Measures
QoL: Quality of Life
SOC: Sense of Coherence
